### Plans to promote participant retention and complete follow-up {18b}

The short duration of the 3-day intervention and the hospital inpatient setting are factors that are expected to promote participant retention. Participants are free to withdraw from the trial at any time and will be made aware that this will not affect their routine medical care. Analysis will be conducted according to an intention-to-treat principle. In the event that participants experience an above-target rise in serum sodium >10mml/L and exit the study to receive re-lowering intravenous dextrose therapy, the primary endpoint will not be reflective of the effect of the intervention. However, it will still reflect the summative effect of pursing that therapy first-line with appropriate safeguards in place. It will therefore still be useful in assessing whether safe correction of sodium is achieved in a timely manner.

### Data management {19}

Data will be collected via direct entry into the Research Electronic Data Capture (REDCap) software database via an application on a password-protected tablet device (Apple iPad) at the participant bedside. This reduces ‘double handling’ of data. Numerical input fields will have range checks for data values to minimize the chance of data entry error. The data will be stored in the secure cloud-based Austin Health REDCap server, with de-identified secure backup copies made weekly.

### Confidentiality {27}

Personal information will be collected only if consent to participate is obtained. Details including name, date of birth, hospital record number and telephone number will be collected to allow the day 34 exit interview to take place. This data will be stored on the secure cloud-based REDCap platform on an Austin Health server. Only authorized study personnel will be granted password-protected access. Participants will be allocated a sequential study identification number for use during the study. Only de-identified information will be published or reported. Electronic and paper study files will be kept for 15 years at which point they will be securely destroyed. Data security will be the responsibility of the primary investigator.

### Plans for collection, laboratory evaluation and storage of biological specimens for genetic or molecular analysis in this trial/future use {33}

Blood and urine biochemistry results will be obtained from samples taken as part of routine hospital care. A sub-study to evaluate serum copeptin before and after intervention to determine if it may predict response to either tolvaptan or fluid restriction is planned, which will require frozen storage of serum samples to be processed at a later date.

## Statistical methods

### Statistical methods for primary and secondary outcomes {20a}

For descriptive data, we will report either mean ± SD or median [IQR] depending on the distribution of the data. Change in serum sodium from baseline (day 1 0600 hours) to day 4 0600 hours (or day of discharge if earlier) will be compared between treatment groups. We will also compare the change in average daily area under the curve (AUC) for the serum sodium concentration from baseline to day 4, in line with analysis performed in the SALT trials [11]. A mixed-effects model based on restricted maximum likelihood (REML) will be used to account for both within-subject variation over time and between-subject variation to assess the treatment effect, namely the mean adjusted difference (MAD) between the control and the tolvaptan group surrounded by a profiled 95% confidence interval. Analysis will be by the intention-to-treat principle (ITT) so that data from participants who withdraw or violate the protocol will be included in their assigned treatment group. We will also perform a per-protocol sensitivity analysis. Plans for the statistical analysis and reporting of each secondary outcome will be decided upon by investigators with access to pooled data.

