### Objectives {7}

Aim: To compare the efficacy and safety of tolvaptan versus a rigorous, protocol-based fluid restriction to raise serum sodium levels in acute hospital inpatients with moderate-to-profound euvolaemic or hypervolaemic hyponatraemia.

Hypothesis: Tolvaptan will be more effective than fluid restriction in raising serum sodium and will lead to faster improvement in hyponatraemia-related symptoms, reduced length of hospital stay, without increasing adverse events.

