### Outcomes {12}

Primary and secondary endpoints are shown in Table 3.

**Table 3 Tab3:** Outcomes

**Primary endpoint**	• Change in serum sodium concentrations over time, from day 1 to day 4
**Secondary endpoints**	• Difference between groups of area under the curve of serial direct serum sodium measurements in mmol/L • Serum sodium increment in the first 24 and 48 h • Proportion of patients normalising serum sodium (defined as serum sodium ≥ 135 mmol/L) • Length of hospital stay • Requirement for serum sodium re-lowering with enteral or IV dextrose/water and/or desmopressin o *Main safety outcome: difference between rates of above-target correction of serum sodium leading to attenuation/reversal therapy (e.g. IV dextrose administration)* • Cognitive and functional measures at 24, 48 and 72 h (or discharge if sooner) o Confusion Assessment Method Shortform (CAM-S) score o Hyponatraemia symptom questionnaire score o Timed Up and Go test score • 30-day readmission rate • Exit questionnaire treatment satisfaction score • Serum sodium concentration 30 days after discharge

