### Sample size {14}

The SALT 1 trial reported a mean difference between tolvaptan and placebo groups in sodium increment at day 4, of approximately 4 mmol/L. The standard deviation (SD) in day 4 sodium concentrations was approximately 4.9 (effect size 0.8). We determined that 2 mmol/L is the minimally clinically relevant difference between tolvaptan and fluid restriction. Using the same SD, we estimated that 64 participants per group would be required to detect this difference based on a *t*-test with 80% power and a 2-sided *p*-value equal to 0.05. To allow for drop-outs including autocorrection of hyponatraemia without specific therapy, a total of 166 participants will be recruited (83 per group).

In case of unforeseen difficulty with recruitment, we have done further power estimates to determine the number of participants required to detect a 3 mmol/L and a 4 mmol/L between group difference, using the same power and significance levels (Table 5). Expected minimum recruitment is 52 participants, or 68 accounting for an additional 30% recruitment margin.

**Table 5 Tab5:** Power calculations

Difference between arms	Number per group	+ 30% to allow for drop-outs and autocorrection	Total sample size
2 mmol/L	64	83	166
3 mmol/L	43	56	112
4 mmol/L	26	34	68

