### Methods in analysis to handle protocol non-adherence and any statistical methods to handle missing data {20c}

Assuming missingness at random (MAR), this is handled by the likelihood-based mixed effects model. In the event of non-missingness at random (NMAR), joint modelling multiple imputation is available as an alternative. As a sensitivity analysis, a per protocol (PP) analysis is performed, including only patients who adhered to the protocol and completed the trial.

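### The primary comparison stops at discharge when that precedes day 4, and participants who overcorrect are said to exit the study, so the plan does not hold to the day-4 difference it names and was sized on

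*Protocol article*

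**What the plan says.** All references are to the protocol article.

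- **Statistical methods {20a}:** the change in serum sodium from day 1 0600 "to day 4 0600 hours (or day of discharge if earlier) will be compared between treatment groups". A REML mixed-effects model then gives the treatment effect, "namely the mean adjusted difference (MAD) between the control and the tolvaptan group". Analysis is by intention to treat, and data from participants who withdraw stay in their assigned group.
- **Outcomes {12}, Table 3:** the primary endpoint is "Change in serum sodium concentrations over time, from day 1 to day 4". No discharge provision is attached to it, although the same table attaches one to the cognitive and functional measures.
- **Sample size {14}:** the starting point is an earlier placebo-controlled trial's "mean difference between tolvaptan and placebo groups in sodium increment at day 4", with 2 mmol/L taken as the smallest relevant difference.
- **Missing data {20c}:** "Assuming missingness at random (MAR), this is handled by the likelihood-based mixed effects model".
- **Objectives {7}:** the hypothesis for tolvaptan includes "reduced length of hospital stay, without increasing adverse events".
- **Retention {18b}:** if participants rise by more than 10 mmol/L and "exit the study to receive re-lowering intravenous dextrose therapy, the primary endpoint will not be reflective of the effect of the intervention". The next sentence adds: "However, it will still reflect the summative effect of pursing that therapy first-line with appropriate safeguards in place".

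**The concern.** Two events can end a participant's contribution before day 4, and both are linked to how sodium responds.

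The first is discharge. If the discharge-day value takes the place of day 4, the outcome mixes changes over different lengths of time. The mix can differ between arms, because the trial itself expects treatment to affect length of stay. The resulting contrast is not the day-4 difference in Table 3 and in the sample size.

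The second is overcorrection. Section {18b} defends the primary endpoint as reflecting the whole strategy, safeguards included. That defence needs the sodium values recorded after re-lowering, and the wording that participants exit the study leaves it open whether those values are used.

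At stake is what the primary estimate means, and whether it can be set against the 2 mmol/L criterion.

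**Working it through.** **1. The day-4 target.** Table 3 and the sample size both point to day 4. Only {20a} adds the discharge alternative. The 2 mmol/L difference is therefore anchored to a time point that not every participant need reach under {20a}.

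The stated 64 per group is a separate matter. With a difference of 2 and SD 4.9, n = 2 × (1.96 + 0.84)² × (4.9/2)² gives about 95 per group, or 96 by an exact t-test, so 64 does not reproduce. This neither supports nor weakens the present point, which concerns the time point only.

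**2. Two rules for one missing value.** A participant who goes home on day 2 or 3 has no day-4 inpatient sodium.

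- Under {20a}, the discharge-day value serves as the end of the comparison.
- Under {20c}, the day-4 value is missing and the likelihood-based model deals with it, assuming missingness at random.

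If the discharge value is labelled day 4, the model sees nothing missing and the rule in {20c} never operates for that participant.

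**3. Direction of any bias.** For each arm (T for tolvaptan, C for fluid restriction):

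- f = share discharged before the day-4 sample
- g = mean further change those participants would have shown by day 4 0600 (positive if still rising)

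Substitution gives

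observed difference = day-4 difference − (f_T × g_T − f_C × g_C).

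The error is zero only if f_T × g_T = f_C × g_C. It lowers the estimate if tolvaptan participants leave earlier while still rising. It raises the estimate if the same happens more on fluid restriction. It is small if early leavers have already normalised. The documents give neither f nor g, so neither sign nor size can be fixed.

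**4. The exit wording.** The sections read side by side:

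- Intervention description {11a} and Table 1: a 24-hour rise above 8 mmol/L means no study intervention that day. The participant stays in the daily schedule.
- Discontinuation criteria {11b}: a rise above 10 mmol/L is a serious adverse event with individualised management. Nothing is said about leaving the study. The sentence on continued standard monitoring belongs to rises that have not exceeded 10 mmol/L, so it does not settle the matter.
- Retention {18b}: participants above 10 mmol/L exit, yet the endpoint reflects the strategy as a whole.
- Statistical methods {20a}: data from withdrawals are kept.

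If sodium through day 4 is used, {18b} is right and the word exit is wrong. If it is not used, the model predicts day 4 from values before re-lowering, which is a different quantity from the one {18b} claims.

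**5. How many the wording could touch.** The background cites overcorrection in 12.1% of registry cases on tolvaptan, and 0 to 30% in observational studies with initial sodium below 125 mmol/L. Applied to 83 per group: 0.121 × 83 ≈ 10, and 0 to 0.30 × 83 ≈ 0 to 25. These rates come from other populations and regimens, so they show possible reach, not an expected number and not a bias.

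**The case against.** **The discharge clause may be harmless.** It can be read as marking the end of observation, with the discharge sodium entering the mixed model at its own time. The text does not say that the value is relabelled or carried forward, and shorter stay as a hypothesis does not show that many leave within 72 hours. This stands in part: substitution is the plain reading, not the only one. But the sentence defines the endpoints of the change being compared, and a clause that admits both readings in the primary analysis needs settling.

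**The article openly addresses overcorrection.** It takes a strategy-wide view, and {20a} retains data from withdrawals. This stands too. A reader might infer that sodium stops being collected at the peak and that the estimate is inflated in favour of tolvaptan. No section says so, and the regimen has earlier dextrose thresholds meant to act before 10 mmol/L. What remains is an unreconciled contradiction.

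**A further inference is not supported.** A reader might take the single mean adjusted difference to be an average over days 2 to 4, and so smaller than the day-4 effect. {20a} does not say that. The same paragraph first defines the comparison as change to day 4, and the model's exact contrast is properly left to an analysis plan.

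**Conclusion.** The point holds for the discharge clause. As written, the primary estimate is a day-4-or-discharge difference. It disagrees with Table 3 and with the basis of the sample size, and it competes with the article's own missing-data rule. The truncating event may depend on treatment and response, so the estimate can be biased in either direction. No size can be given, because the documents contain no early-discharge rate and no sodium course after discharge. A claim of net bias for or against tolvaptan would go beyond them.

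For overcorrection, the point holds only as a contradiction. The exit wording and the strategy-wide claim are compatible only if sodium through day 4 is still collected and analysed. Sections {11a}, {11b}, {18b} and {20a} must be reconciled on this.

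The preference for the mixed model assumes that discharge is explained largely by sodium values already in the model. That is more credible than treating a 24- or 48-hour value as a day-4 value, but it remains an assumption.

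**What to change.** 1. In {20a}, delete the discharge alternative. Define the primary estimate as the treatment contrast at day 4 0600 from the planned mixed model, adjusted for day-1 sodium and the two randomisation strata (volume status, and sodium below or at/above 123 mmol/L).
2. Enter any discharge sodium at the time it was taken. A missing day-4 value is then handled under {20c}.
3. In {18b}, state that leaving the intervention after overcorrection does not end the use of inpatient sodium: values through day 4, including those after re-lowering, enter the intention-to-treat analysis. Align {11a}, {11b} and {20a} with this. It is a data rule only and changes no treatment decision.

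**Cost:** wording and model specification. Sodium is already drawn repeatedly in inpatients, so little or no extra sampling should be needed. The confidence interval will be slightly wider than with substituted values, because day 4 is treated as unobserved in those who have gone home.

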### Interim analyses {21b}

Interim analyses are not planned.

### Methods for additional analyses (e.g. subgroup analyses) {20b}

Subgroup analyses will be performed in a similar mixed-effects model, with respect to effect of volume status (hypervolaemic vs euvolaemic), serum sodium level (mmol/L), urine osmolality (mOsm/kg), urine/plasma osmolality ratio and urine sodium (mmol/L).

### Methods in analysis to handle protocol non-adherence and any statistical methods to handle missing data {20c}

Assuming missingness at random (MAR), this is handled by the likelihood-based mixed effects model. In the event of non-missingness at random (NMAR), joint modelling multiple imputation is available as an alternative. As a sensitivity analysis, a per protocol (PP) analysis is performed, including only patients who adhered to the protocol and completed the trial.

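### Section {20c} offers joint-modelling multiple imputation for data not missing at random, but as stated that method assumes missing at random, so the plan names no analysis that tests departure from that assumption

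*Protocol article*

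**What the plan says.** The main statistical section {20a} sets the primary analysis: "A mixed-effects model based on restricted maximum likelihood (REML) will be used". Section {20c} then deals with missing data in three sentences.

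- Primary assumption: "Assuming missingness at random (MAR), this is handled by the likelihood-based mixed effects model".
- Remedy if that assumption fails: "In the event of non-missingness at random (NMAR), joint modelling multiple imputation is available as an alternative".
- Sensitivity analysis: "As a sensitivity analysis, a per protocol (PP) analysis is performed, including only patients who adhered to the protocol and completed the trial".

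Section {20a} names the same check and no other: "We will also perform a per-protocol sensitivity analysis". Neither section mentions a delta shift, a pattern-mixture, selection or shared-parameter model, or reference-based imputation.

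Three other places bear on how sodium values could go unseen. Section {11d} lets the treating team withdraw a participant for any reason. Section {18b} lets participants withdraw at any time, and describes those with a rise above 10 mmol/L who "exit the study to receive re-lowering intravenous dextrose therapy". Section {17a} states that the trial is open-label.

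**The concern.** Section {20c} pairs a problem with a method that does not address it. Standard joint-modelling imputation fits a multivariate model to the observed data and draws the missing values from it. Unless something is added to make the unseen values differ from what that model predicts, the assumption is MAR, the same one the mixed model makes. If the two analyses were run and agreed, a reader could take the agreement as evidence that the result withstands NMAR, when it would be no such evidence.

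Two further features weaken the sentence. The observed data cannot establish NMAR, so the condition that is meant to call up the alternative can never be seen to be met. And the method is described only as available, which leaves its use to discretion in a trial where allocation is known.

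**Working it through.** The plan gives no missing-outcome rate and no figure for this analysis, so there is nothing of its own to reproduce. The check has three parts.

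**1. Do the two methods differ under NMAR?**

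Inputs from the sample size section {14}: 83 per arm, difference 2 mmol/L, SD 4.9. Assumed, not in the document:
- four daily sodium values with within-patient correlation 0.6;
- mean rise to day 4 of 5 mmol/L (tolvaptan) and 3 mmol/L (fluid restriction);
- day 4 missing in about 25% of the tolvaptan arm, more often when sodium is low, and in 23% of the fluid restriction arm at random.

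Over 1,000 simulated trials, with 20 imputations each and the same variables in both methods, the mean day 4 difference (mmol/L, Monte Carlo standard error about 0.025) was:

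| Missingness depends on | Full data | Likelihood | Joint-model imputation | Completers only |
|---|---|---|---|---|
| observed day 3 value (MAR) | 2.02 | 2.01 | 2.01 | 2.72 |
| unseen day 4 value (NMAR) | 2.01 | 2.68 | 2.68 | 3.21 |

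The likelihood column is the estimate under multivariate normality, standing in for the mixed model. Under NMAR, imputation reproduces the likelihood answer, bias included: 2.68 − 2.01 = 0.67. The size of that bias depends on the assumed mechanism. The agreement between the two columns does not, provided both use the same variables.

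**2. Does the per-protocol analysis fill the gap?**

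It is restricted to those who adhered and completed, and both conditions are determined after randomisation. The completers column shows the completion part alone: it is off by 2.72 − 2.02 = 0.70 under MAR, where the mixed model is right, and by 3.21 − 2.01 = 1.20 under NMAR. Selection on adherence, which means different things for a tablet and a fluid limit, was not simulated and comes on top.

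**3. How much could a departure from MAR move the result?**

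Let p be the fraction missing in an arm and δ the mean amount by which the unseen values differ from their MAR prediction. Then

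true difference − estimated difference = p_T δ_T − p_F δ_F.

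With a departure in one arm only, the shift per 1 mmol/L is p × 1. The departure that would erase a 2 mmol/L effect is 2/p.

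| Missing in that arm (assumed) | Shift per 1 mmol/L departure | Departure that erases 2 mmol/L |
|---|---|---|
| 5% | 0.05 | 2/0.05 = 40 |
| 10% | 0.10 | 2/0.10 = 20 |
| 23% | 0.23 | 2/0.23 = 8.7 |
| 30% | 0.30 | 2/0.30 = 6.7 |

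The 23% row is (83 − 64)/83 = 19/83, the share of recruits covered by the recruitment margin. It is used only as a point on the range.

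With both arms affected, equal departures and equal fractions cancel (0.23 × 1 − 0.23 × 1 = 0), and opposite departures add (0.23 × 1 + 0.23 × 1 = 0.46).

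**The case against.** There is a fair case that this matters little in practice, and much of it stands.

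- **Early discharge does not by itself create a missing endpoint.** Section {20a} defines the comparison as "Change in serum sodium from baseline (day 1 0600 hours) to day 4 0600 hours (or day of discharge if earlier", so a participant discharged early has a value by definition.
- **Exit after a rapid rise may be MAR.** It is triggered by a recorded sodium value, and a likelihood model can use that value. Sections {18b} and {20a} also keep such participants in an intention-to-treat analysis.
- **Sodium is measured often.** Participants are inpatients for 72 h, sampled every 6 to 12 h within routine care. Withdrawal by the participant or the treating team is the main route left to unseen values.
- **The 23% is not a missing-outcome rate.** The margin in {14} covers drop-outs and autocorrection together, and a randomised patient who autocorrects still has sodium measured. A reader might put 23% missing against departures of 1 to 3 mmol/L and conclude that 12% to 35% of the relevant difference is at risk. The document supports neither the fraction nor the departures.
- **Agreement is not guaranteed in every form.** Imputation could bring in auxiliary data that the trial collects, such as interim sodium or urine indices. It could then differ from the mixed model and make MAR more plausible. It would still not be an NMAR analysis.
- **Delta ranges and tipping points usually belong in the analysis plan**, which is not shown. Their absence from an article would not be a finding.

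The last point does not rescue the sentence. The article does not leave the NMAR method open: it names one, and the one named makes the assumption it is supposed to relax. The phrase might loosely mean a joint model of outcome and dropout, or imputation with a shift, but the text says neither.

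**Conclusion.** The sentence in {20c} is wrong as worded. Joint-modelling imputation, as stated, is an MAR method and not an analysis for NMAR, and its trigger cannot be observed. The plan as published therefore names no analysis that tests departure from MAR.

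Two stronger conclusions might be inferred and are not supported. One is that the primary result has no sensitivity analysis at all: the per-protocol analysis does address adherence, and only the missing-data assumption goes unchecked. The other is that the primary result will be biased: NMAR is plausible through withdrawal in an open-label trial, but nothing in the document shows it.

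The size is conditional. For a departure in one arm only, it is 0.05 to 0.30 mmol/L per 1 mmol/L of departure over an assumed 5% to 30% missing in that arm. On those assumptions only a large departure would erase a full 2 mmol/L effect, so the result may well prove robust. The named analyses could not demonstrate it. This should be corrected because the statement is wrong and the correction is cheap; no material effect on this trial has been demonstrated.

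**What to change.** Replace the sentence on NMAR in {20c} with a prespecified sensitivity analysis that is run whatever the data look like:

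- multiple imputation with a delta adjustment added to the imputed sodium values;
- a stated range of deltas, varied separately in each arm;
- the tipping point reported, that is, the delta or pair of deltas at which the conclusion changes.

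Reference-based imputation can be added but is optional. Joint modelling may stay as the imputation engine, provided the text says that without the delta it rests on MAR.

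In {20a} and {20c}, label the per-protocol analysis as an adherence analysis and state that it is not a check on the missing-data assumption.

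The cost is wording in the protocol or analysis plan and a little extra analysis. Conduct, data collection and sample size are unaffected.
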